**Table 6: Guidelines for Subjects Developing Bilirubin Elevations**

| WHO Toxicity Grade            | Ranges                                                                                       | Investigator Action                                                                                                                                                                                                                                                                                                                                              |
|-------------------------------|----------------------------------------------------------------------------------------------|------------------------------------------------------------------------------------------------------------------------------------------------------------------------------------------------------------------------------------------------------------------------------------------------------------------------------------------------------------------|
| Grade 1
Grade 2
Grade 3 | $\geq 1.1$ to $\leq 1.5$ x ULN
$> 1.5$ to $\leq 2.5$ x ULN
$> 2.5$ to $\leq 5.0$ x ULN | May continue intake of investigational medication or have their investigational medication discontinued at the investigator's discretion.
Monitor for progressive increase in bilirubin levels.                                                                                                                                                               |
| Grade 4                       | $> 5.0$ x ULN                                                                                | A confirmatory measurement should be performed within 72 hours after receipt of the results. In case of a confirmed value, the investigational medication should be discontinued (see also Section 10.2) a . PegIFN $\alpha$ -2a and RBV may be continued at the investigator's discretion if increased values are not signs of liver decompensation. |

a Subjects who have known Gilbert's disease and experience isolated grade 4 elevated indirect bilirubin can continue the investigational medication at the investigator's discretion.

#### 9.5.7.4. Clinical Hepatitis

Subjects should be monitored for any worsening of their hepatic disease and development of overt signs and symptoms (including increased fatigue, malaise, anorexia, nausea, dark urine, clay colored stools, bilirubinemia, jaundice, liver tenderness, hepatomegaly, or severely increased serum transaminase levels).

Subjects with these signs and symptoms must seek medical attention immediately and have their hepatic parameters assessed. If severe worsening of hepatic disease is evident, all study medication must be discontinued and the sponsor should be contacted.

#### **9.5.7.5. Other Toxicities Considered to be at Least Possibly Related to TMC435**

Note: For grade 3 or 4 treatment-emergent laboratory abnormalities, subjects should have a confirmatory measurement within 72 hours after receipt of the results. The management scheme below is for confirmed treatment-emergent laboratory abnormalities and not for isolated and/or non-confirmed events.

Note: If the AE or laboratory abnormality is considered “not related” or “doubtfully related” to the investigational medication, the following rules do not apply and the investigational medication may be continued.

For AEs and laboratory abnormalities considered at least possibly related to TMC435, the following rules should be followed (except for the toxicities detailed in Sections 9.5.7.1 to 9.5.7.4).

##### **Grade 1**

Subjects who develop a grade 1 AE or grade 1 laboratory abnormality may continue intake of investigational medication.

##### **Grade 2**

Subjects who develop a grade 2 AE or grade 2 laboratory abnormality may continue or discontinue intake of investigational medication based on the investigator’s clinical judgment.

##### **Grade 3**

Subjects who develop a grade 3 treatment-emergent AE or confirmed grade 3 laboratory abnormality, considered at least possibly related to the investigational medication, must permanently discontinue intake of investigational medication (TMC435) and should be followed as appropriate until resolution of the AE or laboratory abnormality or stabilization (to be agreed upon in collaboration with the sponsor).

##### **Grade 4**

Subjects who develop a grade 4 AE or treatment-emergent confirmed grade 4 laboratory abnormality must permanently discontinue the investigational medication (TMC435) and should be followed as appropriate until resolution of the AE or laboratory abnormality or stabilization (to be agreed upon in collaboration with the sponsor).

#### **9.5.7.6. Toxicity Management for Specific Adverse Events Considered to be at Least Possibly Related to PegIFN $\alpha$ -2a and Ribavirin**

Note: the information below does not imply that the following AEs are caused by PegIFN $\alpha$ -2a or RBV therapy alone, they may also be due to TMC435.

Management of AEs associated with the use of PegIFN $\alpha$ -2a and RBV will be at the discretion of the investigator, taking into account generally accepted medical standards for patient monitoring and management, and the investigator's clinical judgment and clinical practice. General guidance is provided in the sections below. In addition, the manufacturer's prescribing information for PegIFN $\alpha$ -2a (Pegasys) and RBV (Copegus) should be consulted.

#### 9.5.7.6.1. Neuropsychiatric Symptoms

Severe psychiatric symptoms, in particular severe depression (including suicidal ideation or attempts), have been reported with PegIFN $\alpha$ -2a/RBV. These reactions may occur in subjects with and without previous psychiatric illness. Subjects who experience psychiatric symptoms should contact the investigator immediately because discontinuation of study medication may be required. Investigators should refer subjects reporting such symptoms for immediate psychiatric evaluation/medical intervention.

Study medication must be permanently discontinued in case the alterations in personality behavior or mood prevent the subject from performing usual social and functional activities, are associated with behavior potentially harmful to self or others (e.g., suicidal and homicidal ideation or attempt, acute psychosis), or cause inability to perform basic self-care functions; see Table 7 and Section 10.2).

**Table 7: Guidelines for Subjects Developing Psychiatric Symptoms/Depression**

| Severity a | Initial Management
(4-8 weeks)                                                                                                                                                                                                                                                                                                            | Evolution of symptoms                                              |                                                                                                                                        |                                  |
|-----------------------|----------------------------------------------------------------------------------------------------------------------------------------------------------------------------------------------------------------------------------------------------------------------------------------------------------------------------------------------|--------------------------------------------------------------------|----------------------------------------------------------------------------------------------------------------------------------------|----------------------------------|
|                       |                                                                                                                                                                                                                                                                                                                                              | Remains stable                                                     | Improves                                                                                                                               | Worsens                          |
| Mild                  | May continue study medication or have their study medication discontinued at the investigator's discretion.
Evaluate once weekly by visit and/or phone.                                                                                                                                                                                   | Continue weekly visit schedule.                                    | Resume normal visit schedule.                                                                                                          | See grade 2 or grade 3 symptoms. |
| Moderate              | May continue study medication or have their study medication discontinued at the investigator's discretion.
When study medication is continued, reduce to PegIFN $\alpha$ -2a dose to 135 $\mu$ g (in some cases, a second dose reduction to 90 $\mu$ g may be needed).
Evaluate once weekly (office visit at least every other week). | Consider psychiatric consultation.

Continue reduced dosing. | If symptoms improve and are stable for 4 weeks, may resume normal visit schedule.
Continue reduced dosing or return to normal dose. | See grade 3 symptoms             |
| Severe                | Permanently discontinue PegIFN $\alpha$ -2a b (see Section 10.2).
Obtain immediate psychiatric consultation.                                                                                                                                                                                                                   | Psychiatric therapy necessary.                                     |                                                                                                                                        |                                  |

a Refer to the Diagnostic and Statistical Manual of Mental Disorders – fifth edition (DSM-V) for definitions.

b In case PegIFN $\alpha$ -2a has to be discontinued, TMC435 and RBV must be discontinued as well.

### 9.5.7.6.2. Anemia

RBV may cause hemolytic anemia, and PegIFN $\alpha$ -2a can suppress bone marrow production of RBCs. Anemia can be serious and subjects should be monitored closely. Anemia should be managed with RBV dose adjustments and general guidelines for RBV dosage modifications (Table 8).

If RBV dose reductions are insufficient for management of anemia, discontinuation of the investigational medication should be considered. If RBV is discontinued for the management of anemia, TMC435 should be discontinued as well. RBV may be restarted per the dosing modification guidelines. Adjustment of the investigational medication dose is not allowed. Use of erythropoiesis-stimulating agents is not disallowed.

**Table 8: Guidelines for Subjects Developing Anemia**

| Laboratory values                                             | Reduce only RBV dose to 600 mg/day a if hemoglobin level is                             | Discontinue RBV b if hemoglobin level is |
|---------------------------------------------------------------|----------------------------------------------------------------------------------------------------|-----------------------------------------------------|
| Hemoglobin in subjects with no cardiac disease                | < 10 g/dL                                                                                          | < 8.5 g/dL                                          |
| Hemoglobin in subjects with history of stable cardiac disease | $\geq 2$ g/dL decrease in hemoglobin during any 4-week treatment period (permanent dose reduction) | < 12 g/dL despite 4 weeks at reduced dose           |

a One 200 mg tablet in the morning and two 200 mg tablets in the evening.

b If the abnormality is reversed, RBV may be restarted at 600 mg daily and increased further to 800 mg daily at the discretion of the treating physician. However, returning to higher doses is not recommended. If RBV has to be discontinued, TMC435 must be discontinued as well; PegIFN $\alpha$ -2a may be continued at the investigator's discretion.

### 9.5.7.6.3. Hyperglycemia

**Grade 3, 13.89-27.75 mmol/L (251-500 mg/dL); Grade 4, > 27.75 mmol/L (> 500 mg/dL)**

Management decisions must be based on fasted results. If elevated glucose levels are from a non-fasting blood draw, repeat the draw after a 10-hour fast. Subjects with persistent grade 3 or 4 glucose elevations despite anti-hyperglycemic treatment should be permanently discontinued with the exception of subjects with pre-existing diabetes. Appropriate clinical management of hyperglycemia must be started in a timely fashion.

### 9.5.7.6.4. Renal Complications

Renal safety will be monitored by evaluating serum creatinine levels, estimate CLCr (according to the formula derived from the MDRD study and serum chemistry results. The investigator should closely monitor for disturbances in serum creatinine. If renal complications develop, subjects must be treated as clinically appropriate. The study medication may be continued if the renal complication is considered not to be related to the study medication in the opinion of the investigator. RBV should be discontinued in subjects with creatinine > 2mg/dL or CLCr < 50 mL/min.

### 9.5.7.6.5. Decreased White Blood Cell Count

PegIFN $\alpha$ -2a may suppress bone marrow production of leukocytes. General guidelines for PegIFN $\alpha$ -2a dosage modification are provided in Table 9. Use of leukopoiesis-stimulating agents is not disallowed.

**Table 9: Guidelines for Subjects Developing Decreased White Blood Cell Count**

| Laboratory values              | PegIFN $\alpha$ -2a dose | Discontinue PegIFN $\alpha$ -2a a if                                                                                                          |
|--------------------------------|--------------------------|----------------------------------------------------------------------------------------------------------------------------------------------------------|
| ANC $\geq$ 750/mm  | Maintain 180 $\mu$ g     | ANC < 500/mm  ; treatment should be suspended until ANC values return to > 1000/mm  . Reinstitute at 90 $\mu$ g and monitor ANC. |
| ANC < 750/mm       | Reduce to 135 $\mu$ g    |                                                                                                                                                          |

ANC = absolute neutrophil count

a In case PegIFN $\alpha$ -2a has to be discontinued, TMC435 and RBV must be discontinued as well.

### 9.5.7.6.6. Decreased Platelet Count

Platelet counts may drop in the setting of PegIFN $\alpha$ -2a and RBV therapy, due at least in part to PegIFN $\alpha$ -2a suppression of platelet production in the bone marrow. General guidelines for PegIFN $\alpha$ -2a dosage modification is provided in Table 10.

**Table 10: Guidelines for Subjects Developing Decreased Platelet Count**

| Laboratory values                            | PegIFN $\alpha$ -2a dose | Discontinue PegIFN $\alpha$ -2a a if |
|----------------------------------------------|--------------------------|-------------------------------------------------|
| Platelet count $\geq$ 50,000/mm  | Maintain 180 $\mu$ g     | Platelet count < 25,000/mm          |
| Platelet count < 50,000/mm       | Reduce to 90 $\mu$ g     |                                                 |

a In case PegIFN $\alpha$ -2a has to be discontinued, TMC435 and RBV must be discontinued as well.

### 9.5.7.6.7. Thyroid Abnormalities

PegIFN $\alpha$ -2a therapy can be associated with changes in thyroid function, with both hypo- and hyperthyroidism occurring. Such changes are more common in subjects with a history of thyroid dysfunction.

Serum TSH levels should be checked before, during, and after therapy. T3 and free T4 levels should be assessed if changes in TSH values are noted. Subjects should be evaluated by a clinician if biochemical thyroid abnormalities are noted.

Therapy can be stopped and thyroid hormone replacement can be initiated if indicated.

## 9.6. Sample Collection and Handling

The actual dates and times of sample collection must be recorded in the CRF and laboratory requisition form.

Refer to the Time and Events Schedule for the timing and frequency of all sample collections.

Instructions for the collection, handling, storage, and shipment of samples are found in the laboratory manual that will be provided. Collection, handling, storage, and shipment of samples must be under the specified, and where applicable, controlled temperature conditions as indicated in the laboratory manual.

## **10. SUBJECT COMPLETION/WITHDRAWAL**

### **10.1. Completion**

A subject will be considered to have completed the study if he or she has completed assessments at:

- Week 36 for subjects receiving treatment for a total duration of 12 weeks;
- Week 48 for subjects receiving treatment for a total duration of 24 weeks;
- in case of premature discontinuation of all study medication, refer to Time and Events Schedule - Part 4.

### **10.2. Discontinuation of Study Treatment**

If a subject's study treatment must be discontinued before the end of the treatment regimen, this will not result in automatic withdrawal of the subject from the study.

At the discretion of the investigator, all study medication (TMC435, PegIFN $\alpha$ -2a and RBV) may be discontinued for any of the following reasons:

- An SAE occurs.
- The subject fails to comply with the protocol or study staff requirements.

All study medication (TMC435, PegIFN $\alpha$ -2a and RBV) must be discontinued for any of the following reasons:

- withdrawal of consent.
- The subject meets a virologic stopping criterion at Week 4 or 12 or experiences viral breakthrough at any time point during treatment (see Section 6.3).
- The investigator believes that for safety reasons (e.g., AE) it is in the best interest of the subject to discontinue study treatment.
- The subject becomes pregnant.
- A subject fails to comply with the contraception requirements (in female subjects; refer to Section 4.3).
- The subject experiences a grade 3 or 4 rash/allergic reaction (see Sections 9.5.7.1 and 9.5.7.2).
- The subject experiences severe worsening of hepatic disease (see Section 9.5.7.4).

Subjects must discontinue investigational medication (TMC435) and may continue PegIFN $\alpha$ -2a and/or RBV alone if:

- They require treatment with one of the medications included in the list of disallowed concomitant medications (see Section 8).

- The subject experiences grade 4 ALT/AST elevations  $> 2 \times$  baseline value and concurrent grade 4 bilirubin values and the ALT/AST and bilirubin values continue to meet grade 4 criteria at re-testing performed 72 hours after receipt of the results (see Section 9.5.7.3).
- The subject experiences a grade 3 or 4 AE (other than the rash/allergic reaction AE mentioned above) or confirmed grade 3 or 4 laboratory abnormality (other than grade 3 isolated increases in AST/ALT or bilirubin) considered to be at least possibly related to TMC435 (2 consecutive measurements no more than 72 hours after receipt of first results). This excludes AEs or laboratory abnormalities that are not considered to be at least possibly related to TMC435. Subjects who have known Gilbert's disease and experience isolated grade 4 elevated indirect bilirubin can continue the investigational medication at the investigator's discretion.

If a subject discontinues study treatment before the end of the treatment regimen, end-of-treatment and follow-up assessments should be obtained and scheduled assessments should be continued as outlined in Time and Events Schedule - Part 4.

The date and the reason for treatment discontinuation must be noted on the eCRF.

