| Rationale: Clarification of treatment guidelines in case of specific PegIFN-related AEs to make it clear that RBV monotherapy is not allowed.                                                                                                                                                                                                     |                                                                                                                                                                                                                 |
| 9.5.7.6.1
Neuropsychiatric
Symptoms;
9.5.7.6.5 Decreased
WBC
9.5.7.6.5 Decreased
platelets                                                                                                                                                                                                                                             | Stated explicitly that if PegIFN $\alpha$ -2a has to be discontinued for management of the AE, then TMC435 and RBV must also be discontinued                                                                    |

| Applicable Section(s)                                                                                                                                              | Description of Change(s)                                                                                                |
|--------------------------------------------------------------------------------------------------------------------------------------------------------------------|-------------------------------------------------------------------------------------------------------------------------|
| Rationale: Correction of an error: both male and female subjects must discontinue study medication if they fail to comply with contraception requirements   |                                                                                                                         |
| 1.3.5 Overall benefit/risk assessment                                                                                                                              | Deletion of erroneous text                                                                                              |

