### **1.5.5. Overall Benefit/Risk Assessment**

Based on the available data and proposed safety measures, the overall risk/benefit assessment for this clinical study is acceptable for the following reasons:

- Safety data from Phase 1, 2, and 3 studies showed that TMC435 was generally safe and well tolerated in healthy and HCV-infected adults at all doses tested, including the 150 mg once daily dose that is currently used in the ongoing Phase 3 studies.
- Only subjects who meet all of the inclusion criteria and none of the exclusion criteria (as specified in the protocol) will be allowed to participate in this study. The selection criteria

include adequate provisions to minimize the risk and protect the well-being of subjects in the study.

- Safety will be closely monitored by the investigator throughout the study. Safety and tolerability assessments (including vital signs, physical examination, and clinical laboratory tests) will be performed at scheduled visits throughout the study. Adverse events will be monitored from signing of the informed consent onwards until 4 weeks after last study medication intake. Thereafter, only AEs considered related to TMC435 will be reported. SAEs will be reported until 30 days after last study-related procedure.
- Several safety measures have been proposed to minimize potential risk to subjects, including:
  - The safety monitoring and toxicity management plan in this study (see Section 9.5.7) takes into account the known toxicities of the PI class, the safety and tolerability profile of TMC435 as determined in studies in healthy subjects and in (ongoing) studies in HCV-infected subjects, the findings in nonclinical studies, and the safety and tolerability profile of PegIFN $\alpha$ -2a and RBV.
  - Subjects must discontinue all study medication (TMC435, PegIFN $\alpha$ -2a and RBV) for any of the following reasons:
    - withdrawal of consent.
    - The subject meets a virologic stopping criterion at Week 4 or 12 or experiences viral breakthrough at any time point during treatment (see Section 6.3).
    - The investigator believes that for safety reasons (e.g., AE) it is in the best interest of the subject to discontinue study treatment.
    - The subject becomes pregnant.
    - The subject fails to comply with the contraception requirements (refer to Section 4.3).
    - The subject experiences a grade 3 or 4 rash/allergic reaction (see Sections 9.5.7.1 and 9.5.7.2).

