### **4.3. Prohibitions and Restrictions**

Potential subjects must be willing and able to adhere to the following prohibitions and restrictions during the course of the study to be eligible for participation.

Significant teratogenic and/or embryocidal effects have been shown in animals exposed to RBV. Ribavirin may persist in non-plasma compartments for as long as 6 months. It is contraindicated in women who are pregnant or breastfeeding and in male partners of women who are pregnant. In addition, extreme care must be taken to avoid pregnancy in female subjects and in female partners of male subjects taking RBV for at least 6 months after completion of PegIFN $\alpha$ -2a/RBV therapy (or longer, if dictated by local regulations). Ribavirin should not be started unless a report of a negative pregnancy test is obtained immediately prior to initiation of therapy. Therefore, the following precautions must be adhered to:

1. A woman of childbearing potential who is heterosexually active must remain on two different highly effective methods of birth control (see inclusion criteria in Section 4.1) from screening and up to 6 months after the last dose of RBV (or longer if dictated by local regulations).
2. A woman using oral contraceptives must use an additional birth control method (see inclusion criterion in Section 4.1).
3. A man who is sexually active with a woman of childbearing potential and has not had a vasectomy must agree to use two different highly effective methods of birth control (including at least one barrier method). A man who is sexually active with a woman of childbearing potential and has had a vasectomy must agree to use a barrier method of birth control e.g., either condom with spermicidal foam/gel/film/cream/suppository or partner with occlusive cap (diaphragm or cervical/vault caps) with spermicidal foam/gel/film/cream/suppository. All men must also not donate sperm during the study and for 6 months (or longer if dictated by local regulations) after the last dose of RBV.

For male subjects, it is the responsibility of the subject to ensure that his partner (or partners) is (are) not pregnant prior to entry into the study or becomes pregnant during the treatment and post-therapy follow-up phase of the study. During treatment with RBV, female partners of male participants should follow the guidelines as outlined in the manufacturer's prescribing information for RBV.

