### **12.3.3. Pregnancy**

All initial reports of pregnancy must be reported to the sponsor by the study-site personnel within 24 hours of their knowledge of the event using the appropriate pregnancy notification form. Abnormal pregnancy outcomes (e.g., spontaneous abortion, stillbirth, and congenital anomaly) are considered SAEs and must be reported using the Serious Adverse Event Form. Any subject who becomes pregnant during the study must discontinue further study treatment.

In case the partner of a male subject becomes pregnant, the male subject must abstain from sex with that female partner during the pregnancy. It is highly recommended that pregnancies in partners of male subjects included in the study are reported by the investigational staff within 24 hours of their knowledge of the event using the appropriate pregnancy notification form. In view of the privacy regulations, a separate consent of the partner will be obtained at that time.

Follow-up information regarding the outcome of the pregnancy and any postnatal sequelae in the infant will be required.

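### Section 10.2 limits the mandatory stop for contraception non-compliance to women, while Section 1.5.5 applies it to every subject

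*Protocol*

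**What the plan says.** Section 1.5.5 (Overall Benefit/Risk Assessment) lists measures that limit risk to subjects. Among them is a set of reasons for which all three drugs must be discontinued, and one of these is "The subject fails to comply with the contraception requirements (refer to Section 4.3", with no restriction by sex.

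Section 10.2 (Discontinuation of Study Treatment) repeats the mandatory list, but its contraception item is "A subject fails to comply with the contraception requirements (in female subjects; refer to Section 4.3". Just above it, Section 10.2 has a second, discretionary list of reasons for which the investigator may stop all study medication. One of these is "The subject fails to comply with the protocol or study staff requirements".

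Section 4.3 (Prohibitions and Restrictions), to which both contraception items refer, sets requirements for men as well as women. Where the partner could become pregnant, the duty on the man is worded as follows: "has not had a vasectomy must agree to use two different highly effective methods of birth control (including at least one barrier method". Vasectomized men must use a barrier method, and no man may donate sperm during the study or for 6 months after the last ribavirin dose. On ribavirin, the same section says: "It is contraindicated in women who are pregnant or breastfeeding and in male partners of women who are pregnant".

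Section 12.3.3 (Pregnancy) deals with a pregnant partner as follows: "In case the partner of a male subject becomes pregnant, the male subject must abstain from sex with that female partner during the pregnancy". Its requirement to stop treatment is addressed to a subject who becomes pregnant.

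**The concern.** Two current sections give the same safety stopping rule with different scope. Section 1.5.5 makes the stop mandatory for everyone and counts it among the measures that make the benefit/risk balance acceptable. Section 10.2, the section headed as the discontinuation rules and the one that the toxicity guidance in Section 9.5.7 refers to, makes it mandatory only for women.

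The stake is fetal exposure to ribavirin through a male subject. Section 4.3 reports significant teratogenic and/or embryocidal effects in animals and persistence in non-plasma compartments for as long as 6 months. A site that works from Section 10.2 could keep a man on ribavirin after he has stopped meeting his contraception duties and believe it was following the protocol. The duty on men is clear. What differs between the sections is the consequence of breaching it.

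**Working it through.** No figure is involved, so the check is a comparison of the text.

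**Step 1: the two mandatory lists, item by item.**

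| Reason for stopping all study medication | Section 1.5.5 | Section 10.2 |
|---|---|---|
| Withdrawal of consent | yes | same words |
| Virologic stopping criterion or viral breakthrough | yes | same words |
| Investigator's judgment on safety | yes | same words |
| Subject becomes pregnant | yes | same words |
| Contraception non-compliance | any subject | female subjects only |
| Grade 3 or 4 rash or allergic reaction | yes | same words |
| Severe worsening of hepatic disease | yes | same words |

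Each list has 7 items; 6 match word for word and 1 differs in scope (7 − 6 = 1). Apart from the opening article, the only change in that item is the inserted restriction to female subjects.

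**Step 2: does the restriction remove anyone?** It would be harmless if Section 4.3 placed duties on women only. It does not: its third numbered item is addressed to men, and inclusion criterion 10 in Section 4.1 repeats it. The restriction therefore excludes a group that the cited section covers.

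**Step 3: what is left for a non-compliant man in Section 10.2?**

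- The discretionary item on failing to comply with the protocol applies to him, but the investigator may choose not to act on it.
- The mandatory item on safety reasons depends on what the investigator believes is in the subject's own best interest. The harm here falls on a partner and a fetus, so the item does not clearly apply.
- The mandatory item on pregnancy concerns a subject who becomes pregnant.

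**Step 4: does a section other than these two supply the stop?** Section 12.3.3 asks a man with a pregnant partner to abstain from sex with her and does not require him to stop treatment. The ribavirin contraindication in Sections 1.5.4 and 4.3 concerns men whose partners are already pregnant. Neither covers a contraception breach without pregnancy.

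**Step 5: which version is intended?** The rationale recorded for Amendment INT-1 in the Protocol Amendments section says that "both male and female subjects must discontinue study medication if they fail to comply with contraception requirements". The entry reports a deletion of erroneous text in the benefit/risk section, then numbered 1.3.5, and does not list Section 10.2. The log describes earlier text and is used here only as evidence of intent. The discrepancy itself lies between Sections 1.5.5 and 10.2 as they now stand.

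**The case against.** The strongest reply is that the two sections do not strictly contradict each other. Section 10.2 does not say that non-compliant men may continue. Its mandatory item is silent about them, and its discretionary item allows them to be stopped. Section 1.5.5 is current, mandatory text, so a site bound by the whole protocol must stop the man, and a site that does so satisfies both sections. That is correct. It means the protocol as a whole does not leave the matter open; Section 10.2 read alone does. It does not remove the defect, because Section 10.2 is where a site would look for discontinuation rules, and it gives the weaker one.

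A second reply is that the most dangerous case is already controlled. If a partner becomes pregnant, continuing ribavirin conflicts with the contraindication stated in the protocol and with the requirement to give Copegus according to its prescribing information. This stands and narrows the gap. It does not close it, since the purpose of the contraception rule is to act before a pregnancy occurs.

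A third reply is that the point is editorial: intent is on record, men's duties are clear, and no analysis is touched. The absence of any statistical effect is accepted. Against an editorial rating, this is a safety stopping rule for a teratogenic drug, and the wording changes who must be stopped.

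**Conclusion.** The concern holds. One of the seven mandatory stopping items is narrower in Section 10.2 than in Section 1.5.5, and the group left out, men, has explicit duties under the section both items cite. For a man in breach, Section 10.2 turns a required stop into a discretionary one.

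The practical reach is small and cannot be quantified from the protocol. It covers men who breach the contraception requirements on treatment, without a partner pregnancy, at a site that relies on Section 10.2 and whose investigator does not use the discretionary stop. There is no consequence for the primary endpoint, alpha, power or the analysis population. The conclusion rests only on the current wording of Sections 1.5.5, 4.3, 10.2 and 12.3.3. The amendment rationale adds confidence about the direction of the correction. It should be fixed.

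**What to change.** In the mandatory list of Section 10.2, delete the three words restricting the contraception item to female subjects, together with their semicolon, so that the stop covers men and women as in Section 1.5.5. Do not resolve the mismatch the other way by narrowing Section 1.5.5: that would contradict the intent stated for Amendment INT-1 and weaken a measure on which the benefit/risk assessment relies. Notify sites of the corrected text.

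The cost is the deletion of one phrase, with either a clarification letter or inclusion in the next amendment. No visit, assessment or analysis changes.
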